## Statistical methods

### Statistical methods for primary and secondary outcomes {20a}

Demographic and other baseline data including cancer-related clinical characteristics will be listed and summarized descriptively by intervention arm (THI and UC). Categorical data will be presented as frequencies and percentages. For continuous data, mean, standard deviation, median, minimum, and maximum will be presented. For selected parameters, 25th and 75th percentiles will also be presented.

Intention to treat (ITT) analysis will be performed for all participants who enrolled and randomly allocated to one of the clinical trials arms. Descriptive statistics will be used to summarize the original scores for the outcomes (oral and systemic health outcomes), as well as change from baseline, at each scheduled assessment timepoint for the THI and UC group. Additionally, change from baseline in the scale and subscale values at the time of each assessment will be summarized. Participants with an evaluable baseline score and at least one evaluable post baseline score during the treatment period will be included in the change from baseline analyses. The significance of the difference in mean scores between the two arms will be assessed using paired t-test or Wilcoxon signed-rank test. In addition, for each outcome measure, analysis of covariance (ANCOVA) models will be fit to evaluate the difference in mean scores at each timepoint post-baseline with baseline scores as concomitant variables. Repeated measures ANOVA models will be used to examine mean differences in the scores of image-rated oral mucositis, image rated gum inflammation, blood biomarkers of systemic inflammation, and oral and overall quality of life between the THI and UC arms. The differences in least square means between the treatment arms and corresponding 95% confidence interval at selected timepoints will be presented. The Bonferroni method will be used to adjust models for multiple testing.

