### Trial design {8}

Facilitated Lessons on Oral and Systemic Health in Survivors (FLOSS) is a 2-arm, parallel group, 1:1 allocation, superiority randomized controlled trial.

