### Sample size {14}

A power analysis was conducted using effect sizes for telehealth-delivered, psycho-behavioral interventions in cancer survivors. A 6-month study by Abrahams et al. (2017) examining the efficacy of an internet-based cognitive behavior therapy intervention for breast cancer survivors reported mean quality of life of 77.1 (SD = 16.5) and 63.9 (SD = 20.1) for intervention arm and care as usual arm, respectively. This translates to an effect size (standardized mean difference) of 0.71 standard deviations. Based on this finding, we determine sample size for selected power levels and the standardized mean difference (Cohen’s *d*) between the telehealth and usual care arms of the study in the neighborhood of 0.71 standard deviations. Table 3 below presents sample sizes per arm required for selected values of Cohen’s *d* at level of significance, α = 0.05.

**Table 3 Tab3:** Sample sizes per group for selected power and effect size

Power	Effect size (Standardized mean difference)					
	0.30	0.40	0.50	0.60	0.70	0.80
80%	175	99	64	45	33	26
90%	234	132	85	59	44	34

For this study, we will recruit 100 subjects (50 subjects per arm) and expect to detect a medium effect size of approximately 0.60 standard deviations (Cohen’s *d* = 0.60) with 80% power, allowing for an attrition rate of 10%. Of note, sample size will not be adjusted during this trial. Results from this trial will help determine sample size for a larger trial.

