## Assignment of interventions: allocation

### Sequence generation {16a}

Following completion of baseline assessments, participants will be randomly assigned, in a 1:1 ratio, to either the THI or UC arm. A computer-based randomization sequence will be generated by the first author. Intervention allocations will be placed in a password protected folder and stored electronically on university-approved servers (i.e., Box). The study coordinator will examine the randomization allocation on the day of the consent visit and inform participants of their group allocation at the conclusion of their baseline visits and assign participants to group based on these numbers.

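### The tests named for the difference between arms (paired t-test, Wilcoxon signed-rank) need pairs, and this parallel-group trial has none

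*Protocol article*

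**What the plan says.** Section {8} of the protocol article describes a "2-arm, parallel group, 1:1 allocation, superiority randomized controlled trial". Under section {16a}, "participants will be randomly assigned, in a 1:1 ratio, to either the THI or UC arm". Neither section describes matching or any other link between a participant in the telehealth arm (THI) and one in usual care (UC).

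Section {20a} then sets out three analyses of the outcomes, in this order:

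1. "The significance of the difference in mean scores between the two arms will be assessed using paired t-test or Wilcoxon signed-rank test".
2. As an addition, for each outcome measure, "analysis of covariance (ANCOVA) models will be fit to evaluate the difference in mean scores at each timepoint post-baseline", with the baseline score as covariate.
3. "Repeated measures ANOVA models will be used to examine mean differences in the scores" between THI and UC, for the image ratings, inflammatory markers and quality of life.

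The section also promises least-squares mean differences between arms with 95% confidence intervals, and a Bonferroni adjustment. It does not say which of the three analyses decides the question.

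Section {14} sizes the trial on a standardised mean difference between the two arms "at level of significance, α = 0.05".

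**The concern.** A paired t-test and a Wilcoxon signed-rank test are both one-sample tests on within-pair differences. They apply when each observation in one set has a natural partner in the other. Here the two sets are different people, allocated independently. The mismatch covers both the parametric and the non-parametric option, so neither alternative rescues the sentence.

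An analyst who follows the sentence has two ways to make it run:

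- **Pair THI with UC participants by some arbitrary rule**, such as row order. The result then depends on that rule, and any unpaired participant is lost.
- **Test baseline against follow-up within each arm.** This is a natural slip, since the note to Table 1 gives change from baseline as the analysis metric. It tests change over time and not the difference between arms.

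What is at stake is the p-value reported for the arm comparison. The sentence comes first, it is the one framed as assessing significance, and nothing in the section places it below the two models.

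**Working it through.** **Inputs from the document (section {14}).** 50 recruited per arm, 10% attrition, α = 0.05, 80% power, d = 0.60. Completers: 50 × 0.90 = 45 per arm.

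**Step 1: which test was the trial sized for?** An independent two-sample t-test, two-sided α = 0.05, 80% power and d = 0.60 requires 44.59, so 45 per arm, as in Table 3. Inflating for attrition, 45 / 0.90 = 50, as planned. All 12 cells of Table 3 match the independent-samples calculation rounded to the nearest whole number (for example 175.38 against 175, and 59.35 against 59). A paired test with d taken as the standardised paired difference would need only 24 pairs in the same cell. The sample size was therefore built for independent arms.

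**Step 2: the literal reading, arbitrary pairing across arms.** Take 45 pairs of independent observations.

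- Noncentrality is the same for both tests: 0.60 × √(45/2) = 2.846.
- Independent test: 88 df, power 80.4%.
- Arbitrary pairing: 44 df, power 79.5%.
- Type I error by simulation (20,000 runs, no arm effect): about 5% for both.

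The cost is therefore not error inflation. It is that the p-value changes with the pairing and that the arms must be equal in number. If each of 50 participants per arm independently has a 10% chance of dropping out (an assumption built on the attrition figure in {14}), the completer counts differ with probability 0.87.

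**Step 3: the within-arm reading.** Assumptions, none of which the document gives: change-score SD of 1, no true arm effect, and the same mean improvement δ in both arms. Let p be the power of a one-sample t-test with n = 45, two-sided α = 0.05 and noncentrality δ√45. The arms are independent, so

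P(significant in THI only) = p(1 − p).

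| δ (SD) | p | p(1 − p) |
|---|---|---|
| 0 | 0.050 | 4.8% |
| 0.1 | 0.101 | 9.0% |
| 0.2 | 0.259 | 19% |
| 0.3 | 0.503 | 25% |
| 0.4 | 0.747 | 19% |
| 0.5 | 0.907 | 8.5% |
| 0.6 | 0.976 | 2.4% |

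Simulation with a baseline to follow-up correlation of 0.5, which gives a change SD of 1, agrees: 24.7% at 0.3 SD and 19.1% at 0.4 SD. In the same runs the independent test on change scores rejected in about 5%. The maximum of p(1 − p) is 0.25, at p = 0.5, so the value at 0.3 SD is effectively the worst case.

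**Step 4: does the rest of {20a} compare the arms?** Yes. ANCOVA with baseline as covariate and repeated measures ANOVA between THI and UC both do so, and the planned least-squares mean differences with confidence intervals are between-arm estimates.

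**The case against.** The strongest reply is that this is a slip in naming and that little depends on it. Table 3 fits an independent-samples formula, so the authors evidently planned for independent arms. Two valid between-arm models appear in the same paragraph and would be produced even if the sentence stayed. Equal numbers per arm are also possible, since section {20c} plans multiple imputation, although its exclusion of participants with a new or recurrent cancer could still unbalance the arms. Most of this stands, and it limits the consequence. It does not make the named tests applicable, and the section does not tell the reader to prefer the models.

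Two stronger readings are tempting, and the document supports neither.

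- **That the trial cannot test its hypothesis.** This may be said of the named tests as they would normally be run. It is not true of the plan, because ANCOVA and repeated measures ANOVA compare the arms.
- **That the false-positive rate will be far above 5%.** This requires an analyst to set aside the sentence's own statement that the comparison is between arms, to test within each arm, and then to treat significance in THI alone as efficacy. The protocol never proposes that inference. Even then, the rate depends on an assumed common improvement and falls below 5% at both ends of the range shown.

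**Conclusion.** The sentence is wrong as written and should be corrected. Tests for paired data are named for two independent, unmatched arms, and nothing elsewhere in the article repairs this. An analysis plan that is not shown could depart from the sentence, but it would then contradict the published protocol.

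The damage is bounded. Under the literal reading, type I error stays near 5% and power falls by about one percentage point (80.4% to 79.5%). The defect there is dependence on an arbitrary pairing and the need for equal numbers. Under the within-arm reading, the test answers a different question. The 2% to 25% range applies only if efficacy is inferred from significance in THI alone, with 45 per arm, a change SD of 1 and an equal improvement of 0 to 0.6 SD in both arms. The practical risk is that an inapplicable test supplies the headline p-value, because it is listed first and the analyses are not ranked.

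**What to change.** In section {20a}, replace the paired t-test and Wilcoxon signed-rank test with the two-sample t-test and the Wilcoxon rank-sum (Mann-Whitney) test, and label these as supporting analyses. State that the conclusion about the arm difference rests on the baseline-adjusted between-arm model already specified in that section. Paired tests may remain only as a description of change within each arm, with no claim of efficacy attached.

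This costs a sentence or two in the protocol and the matching wording in any analysis plan. The sample size, data collection and visits do not change. The article gives June 2026 as the end of recruitment; the correction should in any case be made before the outcome data are analysed by arm.

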#### Secondary outcomes

Secondary outcomes of interest are related to systemic health and include systemic inflammation, overall quality of life, and comorbidities. Measures include collection of biospecimen, anthropometrics, and self-report measures. The target endpoint for secondary measures is 6-months, post-randomization.

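### One single-step Bonferroni rule follows a model list that mixes primary and secondary outcomes and gives the primaries no priority; a named 6-month primary family under Holm would serve better at no cost in participants

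*Protocol article*

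**What the plan says.** The Outcomes section {12} names three primary constructs: image-rated oral mucositis, image-rated gingival inflammation and quality of life, with a target endpoint of 6 months. Oral health-related quality of life is measured with two instruments, OHIP-14 and the EORTC oral health module. Systemic inflammation, overall quality of life and comorbidities are secondary, and they share the timing: "The target endpoint for secondary measures is 6-months, post-randomization". The blood markers are CRP, IL-1, IL-6 and TNF-alpha.

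Section {20a} covers both tiers together. Its repeated measures ANOVA is to compare the arms on "image-rated oral mucositis, image rated gum inflammation, blood biomarkers of systemic inflammation, and oral and overall quality of life". The paragraph ends: "The Bonferroni method will be used to adjust models for multiple testing". It gives no divisor, family or order of testing, and it does not say whether secondary results are exploratory.

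The sample size section {14} works "at level of significance, α = 0.05" for a single comparison. It says "we will recruit 100 subjects (50 subjects per arm") and that the investigators "expect to detect a medium effect size of approximately 0.60 standard deviations" with 80% power after 10% attrition.

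**The concern.** The protocol has chosen a procedure, single-step Bonferroni, and an object for it, the models. The models just listed cross the two tiers. Nothing in the text protects the primaries from sharing alpha with the biomarkers and overall quality of life. Nor does anything say that error is to be controlled across the primaries and not merely between timepoints within one model.

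The conclusion can depend on how that sentence is carried out. With 8 tests, for example, the threshold is 0.05/8 = 0.00625, so a primary p-value between about 0.006 and 0.05 would count as positive under one execution and negative under another. Separately, Holm controls the same family-wise error rate as Bonferroni, rejects everything Bonferroni rejects and sometimes more, and needs no further assumption.

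**Working it through.** **Inputs.** From {14}: alpha 0.05, 80% power, effect size d = 0.60, 50 per arm, 10% attrition, so 50 × 0.90 = 45 evaluable per arm. From {12}: three primary constructs (four scores if both oral quality-of-life instruments count), four biomarkers, one overall quality-of-life instrument, and post-baseline visits at 6 and 12 months. Assumed: two-sided tests, the number of tests in the family, and the correlations between outcomes.

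**The plan's own figure.** Two-sample t-test, noncentral t with noncentrality d√(n/2) = 0.60 × √22.5 = 2.85. At two-sided 0.05 and 45 per arm, power is 80.4%. This agrees with the 45 per group in Table 3, and 45/0.90 = 50 enrolled. The two-sided assumption fits: a one-sided 0.05 test would need 36, not 45.

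**Execution over the listed models.** Same formula at alpha 0.05/k:

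| Tests in family (k) | Alpha per test | Power per primary, d = 0.60 |
|---|---|---|
| 1, no adjustment | 0.05 | 80.4% |
| 3, primaries only | 0.0167 | 65.7% |
| 4, primaries with both oral quality-of-life scores | 0.0125 | 61.7% |
| 5, constructs as listed | 0.01 | 58.6% |
| 8 = 3 primaries + 4 biomarkers + overall quality of life | 0.00625 | 52.0% |
| 9, as above with both oral quality-of-life scores | 0.0056 | 50.4% |
| 16 to 18, the last two rows at two timepoints | 0.0031 to 0.0028 | 42.9% to 41.4% |

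At 8 tests, the non-primary tests cost each primary 65.7 − 52.0 = 13.7 percentage points.

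**Execution within each model only.** Family-wise error at 6 months across three primaries with no true effect:

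- Two timepoint contrasts per model, each at 0.05/2 = 0.025. If independent, 1 − 0.975³ = 7.3%. By simulation (1,000,000 draws), about 6.5% at correlation 0.5 and 5.1% at 0.8.
- One contrast per model at 0.05. If independent, 1 − 0.95³ = 14.3%. By simulation, about 12.6% at correlation 0.5 and 9.8% at 0.8.

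**Holm against single-step Bonferroni, primaries only.** Simulated z-statistics with mean 2.85 (normal approximation, 45 per arm, every effect 0.60):

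| Primary scores | Correlation | Bonferroni, average power | Holm, average power |
|---|---|---|---|
| 3 | 0.3 | 67.4% | 75.6% |
| 3 | 0.5 | 67.4% | 75.1% |
| 4 | 0.3 to 0.5 | about 64% | about 73% |

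Both procedures keep the family-wise rate at or below 5%. The Bonferroni figures lie slightly above the 65.7% and 61.7% in the first table because that table uses the t distribution.

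**The case against.** Four objections carry weight.

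- **The pooled list is never called the Bonferroni family.** A reader might infer that it is. The text supports only that the list says which outcomes get repeated measures ANOVA and that the next multiplicity sentence names no family. A combined heading for primary and secondary outcomes is the standard SPIRIT item.
- **The two executions are not the only ones.** Bonferroni over the primaries alone, or separately by tier, also fits the sentence and has neither drawback. {12} does define the tiers. No wording in {20a} points to that execution, though, and it is close to what the fix makes explicit.
- **Error inflation is easy to overstate.** A reader might conclude that within-model adjustment more than doubles the false-positive rate for the primaries. With two contrasts at 0.025 each, the 6-month rate is about 5% to 7%. The 14% figure needs a single contrast at 0.05 and independent outcomes. Pooling over all models inflates nothing; it costs only power.
- **Bonferroni is valid, and families are often defined in an analysis plan.** Both are true. An unstated divisor alone would not be a finding in a condensed article. What remains is that the protocol does commit to a rule, and that rule is less powerful than a free alternative and is written without priority for the primaries.

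It is also fair that the trial's question covers oral and systemic health, so making every systemic outcome exploratory is a design decision and not a formality. The fix therefore offers a gate.

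**Conclusion.** The point holds as a cheap improvement, not as a demonstrated error-rate fault. {20a} sets single-step Bonferroni for models directly after a list that crosses the tiers, and it gives the primaries no priority.

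If the listed models form the family, power per primary falls from 66% (three primaries alone) to about 59%, 52% or 50% with 5, 8 or 9 tests. If adjustment is only within models, error across the three primaries at 6 months ranges from about 5% to about 14%, depending on the number of contrasts and the correlation. Holm on the primaries would gain roughly 8 to 9 percentage points of average power over Bonferroni on the same family.

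These figures assume 45 evaluable per arm, two-sided tests, d = 0.60 (for the Holm comparison, on every primary) and correlations that the protocol does not give. The family sizes are also assumed. The documents do not support saying that the plan pools the tiers, or that the primaries are bound to be either diluted or uncontrolled.

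**What to change.** Replace the Bonferroni sentence in {20a} with text to this effect:

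*The confirmatory family is THI versus UC at 6 months on image-rated oral mucositis, image-rated gingival inflammation and oral health-related quality of life [name one instrument, or list both]. Each comparison takes its p-value from [one named model]. The family is controlled at two-sided 0.05 by the Holm procedure. Secondary outcomes at 6 months are tested as a separate family, also by Holm at 0.05, only if every primary null hypothesis is rejected; otherwise they are exploratory. Comparisons at 12 months are exploratory unless listed in the gated family.*

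Two choices have to be made in the text. The first is whether one or both oral quality-of-life instruments enter the family (three or four scores). The second is which of the analyses in {20a} (the t-test or Wilcoxon test, ANCOVA, or repeated measures ANOVA) supplies the p-value. If the sponsor does not want a gate, labelling all secondary outcomes exploratory, with unadjusted p-values and 95% confidence intervals, is also sound.

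The cost is wording only, with no extra participants or data. No interim analysis is planned, so the change can be made without knowledge of results if it is dated before unblinding. The small downside is that secondary and 12-month results carry no confirmatory claim unless the gate is passed.

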### Interim analyses {21b}

No interim analysis will be conducted.

### Methods for additional analyses (e.g. subgroup analyses) {20b}

We will not conduct subgroup analyses.

### Methods in analysis to handle protocol non-adherence and any statistical methods to handle missing data {20c}

We will employ intent-to-treat method for data analysis to address missing data and protocol nonadherence. In addition, we will examine patterns of missing data over the intervention period, and use multiple imputation to address incomplete data.

If participants receive a new or recurrent cancer diagnoses during the intervention, they will be asked to report it to study personnel. The participant will be able to continue study procedures (i.e., intervention and assessments), but their data will not be included in the final analyses.

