### Eligibility criteria {10}

The study population will comprise 100 unselected cancer survivors, recruited via established community-based approaches. “Unselected’ cancer survivors refer to individuals not selected based on cancer type. With the exception of head and neck cancer, all other cancer sites are eligible for this study. Survivors will be identified via cancer survivorship groups and established community-based approaches (e.g., community outreach programming). The inclusion criteria are: (1) male and female cancer survivors who ≥ 6 months after completion of primary therapy for cancer treatment; (2) greater than 25 years of age, and less than 75 years of age; (3) all race/ethnic groups; and (4) own a smart phone. The exclusion criteria include the following: (1) all head and neck/oral cancers; (2) less than 25 years of age and greater than 75 years of age; (3) recurrence/second cancers; and (4) unable to provide informed consent.

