### Intervention description {11a}

The intervention is grounded in social-cognitive theory, which posits that human behavior is mutually-influenced by person- and environmental-level factors [9]. The FLOSS project is a 6-month telehealth intervention (THI) that provides education on cognitive, behavioral and environmental-level factors that inform oral and systemic health. Participants randomized to THI arm will engage in 6, monthly 1-h virtual sessions with a facilitator training in motivational interviewing. Each session will contain: 1) a participant check-in, 2) content designed to build oral health literacy and self-efficacy, 3) and goal-setting and implementation planning. Participants will complete module handouts on-paper or electronically that reinforces module content. Additionally, participants will also receive biweekly tailored text messages aligned with monthly module content. Post-intervention follow-up will occur at 6- and 12-month post-randomization. See lineup of module topics below:

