### Criteria for discontinuing or modifying allocated interventions {11b}

Participants can withdraw from either study arm voluntarily. Participants randomized to the telehealth intervention group who wish to withdraw from the study will receive the intervention module materials via email or print. We will collect assessment data from participants who discontinue the intervention.

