### Relevant concomitant care permitted or prohibited during the trial {11d}

Treatment for cancer is prohibited during the trial. Participants cannot be undergoing treatment.

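### Randomised participants who report a new or recurrent cancer are removed from the final analyses, which contradicts the stated intention-to-treat analysis

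*Protocol article*

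**What the plan says.** Section 20a of the protocol article defines the analysis population: "Intention to treat (ITT) analysis will be performed for all participants who enrolled and randomly allocated to one of the clinical trials arms". Section 20c repeats the principle: "We will employ intent-to-treat method for data analysis to address missing data and protocol nonadherence". It adds multiple imputation for incomplete data.

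The next paragraph of section 20c sets a different rule for one group. The trigger is "If participants receive a new or recurrent cancer diagnoses during the intervention, they will be asked to report it to study personnel". The consequence is "The participant will be able to continue study procedures (i.e., intervention and assessments), but their data will not be included in the final analyses".

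Four other places bear on this:

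- Eligibility (section 10) lists the same condition as an entry exclusion: "3) recurrence/second cancers; and (4) unable to provide informed consent".
- Section 11d states "Treatment for cancer is prohibited during the trial".
- Section 11b keeps following people who stop the intervention: "We will collect assessment data from participants who discontinue the intervention".
- Table 1 schedules a Cancer Treatment item at 0, 6 and 12 months, without distinction by arm.

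**The concern.** An intention-to-treat set is fixed at randomisation. Here a randomised participant who may still be attending visits and giving data leaves the analysis because of something that happened afterwards. Two analysts following this text could form different primary populations, and results produced under the exclusion could not properly be reported as the analysis that section 20a defines.

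There are two reasons to doubt that the exclusion is neutral.

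- **Relation to outcome.** The Background links cancer treatment to oral mucositis, tissue damage and inflammation. A new cancer may therefore be related to the primary outcomes.
- **Ascertainment.** The event becomes known when the participant reports it. In the telehealth arm, "Participants randomized to THI arm will engage in 6, monthly 1-h virtual sessions with a facilitator training in motivational interviewing", and each session includes a check-in. The usual care arm is described as receiving text messages every two weeks. Staff may therefore learn of events more completely in one arm than in the other.

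The exclusion also removes data from a trial whose sample size leaves no room beyond its attrition allowance.

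**Working it through.** **1. The rules side by side**

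| Topic | Rule | Section |
|---|---|---|
| Who is analysed | Everyone randomised | 20a, repeated in 20c |
| Participant stops the intervention | Assessments still collected | 11b |
| Data incomplete | Multiple imputation | 20c |
| New or recurrent cancer, participant stays | Data excluded from the final analyses | 20c |

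The last row conflicts with the first. It also sits oddly with the other two: values never observed are imputed, while values that can be observed are discarded. The entry exclusion in section 10 may explain the rule, but an eligibility criterion applied after randomisation is still a post-randomisation exclusion. No analysis that retains these participants is described.

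**2. The plan's own sample size**

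Inputs from section 14: d = 0.60, power 80%, α = 0.05 (two-sided reproduces Table 3), attrition 10%.

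- A two-sample t-test needs 44.59 per arm, rounded up to 45. This matches Table 3.
- 45 / (1 − 0.10) = 50 per arm. This matches the planned 100.
- Power with 45 per arm is 0.804.

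The 10% allowance is therefore fully used by ordinary attrition.

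**3. Power after exclusions**

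The documents give no rate of new or recurrent cancer. The fractions x below are assumptions, applied equally to both arms, with n = 45(1 − x).

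| Assumed fraction excluded | n per arm | Power at d = 0.60 |
|---|---|---|
| 0% | 45 | 0.804 |
| 2% | 44.1 | 0.796 |
| 5% | 42.75 | 0.783 |
| 10% | 40.5 | 0.760 |

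This treats the exclusions as additional to attrition. If some of these people would have dropped out anyway, the loss is smaller.

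**4. What unequal detection could do**

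Suppose the true effect is zero, a fraction p of each arm has the event, affected participants score g SD worse, and a fraction s of events is detected and excluded. The share of affected people left in an arm is p(1 − s) / (1 − p·s). The spurious difference is g times the difference in that share between arms. All inputs are assumed, with g from 0.5 to 1.0 SD.

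| p | s in telehealth | s in usual care | Spurious difference (SD) |
|---|---|---|---|
| 5% or 10% | 1 | 1 | 0 |
| 5% | 1 | 0.50 | 0.013 to 0.026 |
| 5% | 1 | 0.25 | 0.019 to 0.038 |
| 10% | 1 | 0.50 | 0.026 to 0.053 |
| 10% | 1 | 0.25 | 0.038 to 0.077 |

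For the last row: 0.10 × 0.75 / (1 − 0.10 × 0.25) = 0.075 / 0.975 = 0.077, times g = 1.0. Against the design effect this is 0.077 / 0.60 = 0.13. The sign follows from assuming better detection in the telehealth arm; swapping the detection fractions reverses it.

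Parts 3 and 4 rest on different reporting assumptions, equal in one and unequal in the other, so the two harms cannot be added together at full size.

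**5. The window**

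Section 20c limits the trigger to the intervention period. Section 11a makes that six months for the telehealth arm. The usual care arm has no sessions, and assessments run to 12 months. The text does not settle what the period means for usual care, or how an event between months 6 and 12 is handled.

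**The case against.** The best defence is that the rule is prespecified, worded identically for both arms, and consistent with a trial meant for people without recurrence. Nothing in the article suggests that oral health education would change cancer incidence within six months. Both arms are asked to report, both are scheduled for the 6-month visit that carries the target endpoint, and Table 1 lists a Cancer Treatment item for that visit. Equal detection is thus quite possible, and in the simple model the bias is then zero.

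This largely disposes of a stronger reading that a reader might infer: that exclusion will be more complete in the telehealth arm, will remove the worst scores, and so will favour the intervention. The documents do not support it. Different contact schedules make unequal ascertainment possible, but no passage says that it will occur, and the shared visit may narrow any gap. The trigger is a diagnosis, not treatment, so someone diagnosed shortly before month 6 may be untreated. The Background puts mucositis at over 40% of survivors during treatment, which is not everyone. No figure in the article fixes how much worse affected participants would score.

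The defence does not touch the contradiction. A prespecified, symmetric exclusion after randomisation is still not an analysis of everyone randomised, and no other section resolves the conflict.

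On sections 11d and 20c, one can fairly say that the first concerns treatment and the second a diagnosis. They meet when a participant with a new cancer starts treatment and continues, and the text does not say what applies then.

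**Conclusion.** The contradiction stands on the text alone and needs no assumed figure. Section 20c removes randomised participants whose data can still be collected, while sections 20a and 20c promise intention to treat.

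The bias is a risk, not a demonstrated effect, and the documents establish neither its size nor its direction. Under the assumed inputs above it runs from zero to 0.077 SD, against a design effect of 0.60 SD. The power loss is also modest: from 0.804 to between 0.796 and 0.760 if 2% to 10% are excluded in both arms on top of 10% attrition. Both ranges are illustrative, because the article gives no event rate. The case for correction rests on who belongs in the primary analysis, not on these numbers.

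**What to change.** 1. Replace the exclusion sentence in section 20c with wording such as: *Participants with a new or recurrent cancer after randomisation remain in the primary intention-to-treat analysis in their allocated arm, with all data collected.*
2. Make exclusion of these participants, or censoring of their data after diagnosis, a labelled sensitivity analysis, and report the number affected by arm.
3. State the event window, either 0 to 6 or 0 to 12 months from randomisation, in the same terms for both arms.
4. Ascertain events by the same question in both arms at the scheduled visits, using the existing Cancer Treatment item in Table 1 and checking that its wording covers a new diagnosis.
5. Reconcile sections 11d and 20c on cancer treatment during the trial and continued participation. Which clinical rule applies is for the investigators to decide.

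The cost is a wording amendment and one sensitivity analysis. No visits are added. The change should be made before the analysts are unblinded.
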